### Data Analysis Plan

The data were analyzed using SPSS v.22 (IBM Corp). Both descriptive statistics (frequency, percentage, mean, and SD) and inferential statistics (multivariate ANOVA) were used. A *P* value less than .05 was considered statistically significant.

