### Trial Design and Study Population

#### Overview

This protocol is for a prospective multicenter randomized clinical trial, which began in March 2025 and is expected to end in November 2025. This protocol outlines our plan to assess the knowledge and skill enhancement of a pilot intervention across three centers: Hasanuddin University (Makassar, Indonesia), Padjajaran University (Bandung, Indonesia), and Universitas Sumatera Utara (Medan, Indonesia). A total of 90 dental students participated in the study (G*Power effect size 0.6, statistical power 85%). All participants enrolled in this study were randomly assigned to either an intervention group (n=15) or a control group (n=15) within each center. We used the block randomization method for the allocation of participants.

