**Assessments**					
	MCQ questionnaires	✓			✓
	Knowledge improvement, posttest scores				✓
	Participants’ satisfaction with IRTS				✓

^a^MCQ: multiple-choice question.

^b^IRTS: Immersive Reality Training System.

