#### Participants’ Performance and Knowledge Improvement

To assess the practical skills and knowledge acquired, participants from both the intervention and control groups will be required to complete a pretest prior to the training and a posttest following the training session. The MCQs were administered in accordance with the reference textbook used by the Faculty of Dentistry, as outlined in the dentistry curriculum [46]. The scores ranged from 0 to 100, and the test scores of both groups were subsequently compared. The MCQs are centered on the procedural steps, instrumentation, and guiding principles pertinent to dental extraction. This examination is an established component of the curricula at Hasanuddin University, Padjajaran University, and Universitas Sumatera Utara, aimed at assessing students’ practical competencies and theoretical knowledge. Consequently, a comparative analysis test will be used to evaluate the scores obtained from the clinical skill training between these two groups.

Additionally, the performance of participants will be evaluated through recorded video training and will be assessed by an independent reviewer, focusing on training time completion, in-app lag or confusion, and skipped steps. The confidential paper-based data of participants will be securely stored in a locked storage unit at the study site, while electronic data will be maintained in a protected folder on a server at Hasanuddin University, Makassar, Indonesia.

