## Discussion

### Strengths and Limitations

This study uses IR technology to advance the training of dental students in dental extraction methods, allowing them to experience immersive, high-fidelity scenarios that closely resemble actual clinical situations. One of the primary strengths of the IR training program is its incorporation of essential procedures for both open and closed extraction. The adaptation and validation process involves a thorough selection procedure conducted in collaboration with engineering experts. Consequently, the findings will offer both quantitative and qualitative perspectives on the enhancement of participants’ abilities. Moreover, the research included dental students from three distinct provinces (West Sumatra, West Java, and South Sulawesi) to provide an in-depth analysis of the potential influence of IR-based training on dental students’ skills in performing tooth extractions.

The presence of a control group in this study enables the observation of improvements in dental students. The pre- and posttest MCQs allow not only comparisons within the same group but also evaluation of the IRTS against traditional methods regarding dental students’ learning outcomes, thereby strengthening the validity of our findings.

In recognizing the strengths of this study, it is equally crucial to address its limitations. A notable concern is the potential for selection bias, as participants may inherently possess a favorable disposition toward technology or virtual reality environments. To mitigate this bias, we have meticulously documented the participants’ prior interactions with virtual reality technology and incorporated this information into experience distribution tables.

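### The only inferential method named, a multivariate ANOVA with no outcomes listed, fits the trial's single between-arm pretest/posttest question poorly; ANCOVA adjusted for pretest and center would fit it better

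*Protocol article*

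**What the plan says.** The Data Analysis Plan names descriptive statistics and one inferential method: "inferential statistics (multivariate ANOVA) were used". The significance rule is a P "value less than .05 was considered statistically significant". Dependent variables, factors and covariates are not listed.

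Under Participants' Performance and Knowledge Improvement, students in both arms are "required to complete a pretest prior to the training and a posttest following the training session". The MCQ score runs from 0 to 100. The same section adds that "a comparative analysis test will be used to evaluate the scores obtained from the clinical skill training between these two groups", without naming the test. Strengths and Limitations says that the two tests "allow not only comparisons within the same group but also evaluation of the IRTS against traditional methods".

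The Overview of the trial design gives the size: "A total of 90 dental students participated in the study (G*Power effect size 0.6, statistical power 85"%). Students are "randomly assigned to either an intervention group (n=15) or a control group (n=15) within each center", which over three centers makes 45 per arm.

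Two questionnaires, described under Participants' Experience and Feedback, ask about the immersive reality system. Table 1 lists the corresponding outcome as "satisfaction with IRTS".

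**The concern.** A trial with one score, two arms and a baseline measurement of that score calls for an estimate of the between-arm posttest difference, made precise by the baseline. A multivariate ANOVA is an omnibus test: it asks whether the arms differ on any combination of its outcomes. If the pretest is one of those outcomes, part of the test is spent on a difference that training cannot have caused, because the pretest comes before training. A significant result then does not say which score differed, and the test itself gives no single adjusted effect.

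At stake are the interpretability of the main result and some power. Because the outcomes are not listed, two analyses with different properties both fit the text.

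**Working it through.** **Inputs.** From the protocol: 45 per arm, effect size 0.6, power 85%, significance level 0.05. Assumed, because the protocol does not say: 0.6 is Cohen's d on the posttest, the test is two-sided, there is no true pretest difference, and the pretest-posttest correlation ρ is 0.3, 0.5 or 0.7.

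**The protocol's own figure.** A two-sided two-sample t test with d = 0.6 and 85% power needs 102 students (100 by the normal approximation). With 90 it has 80.4% power. One-sided, it needs 82, and 90 students give 88.1%. The stated 90 is not reproduced exactly either way. The test behind it is not stated, so it does not show which analysis was intended.

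**Reading 1: pretest and posttest as joint outcomes.** With two arms this is Hotelling's T². The squared distance between arms is D² = d²/(1 − ρ²) and the noncentrality is λ = (45/2) × D², referred to F(2, 87).

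**ANCOVA.** Posttest on arm with pretest as covariate has the same λ, referred to F(1, 87).

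**Reading 2: group by time.** This is a test on change scores. The standardized effect is d/√(2(1 − ρ)), so λ = (45/2) × d²/(2(1 − ρ)), referred to F(1, 88).

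| ρ (assumed) | λ, joint MANOVA and ANCOVA | Joint MANOVA | ANCOVA | λ, change score | Group by time |
|---|---|---|---|---|---|
| 0.3 | 22.5 × 0.36/0.91 = 8.90 | 75.0% | 83.9% | 22.5 × 0.36/1.4 = 5.79 | 66% |
| 0.5 | 22.5 × 0.36/0.75 = 10.80 | 83.2% | 90.1% | 22.5 × 0.36/1.0 = 8.10 | 80% |
| 0.7 | 22.5 × 0.36/0.51 = 15.88 | 94.9% | 97.6% | 22.5 × 0.36/0.6 = 13.50 | 95% |

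The joint MANOVA therefore loses 83.9 − 75.0 = 8.9, 90.1 − 83.2 = 6.9 and 97.6 − 94.9 = 2.7 points. Since λ is the same, the whole loss is the extra numerator degree of freedom. For 85% power the joint MANOVA needs 114, 96 and 66 students in total, and ANCOVA needs 94, 78 and 54. At ρ = 0.5 the joint MANOVA needs about 110 students to match ANCOVA with 90.

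Adding center as a three-level factor costs ANCOVA two residual degrees of freedom. With F(1, 85) and the same λ, power is still 83.9%, 90.1% and 97.6%, before counting any variance that center explains.

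**Chance pretest imbalance under reading 1.** These are simulated rejection rates with no training effect, 20,000 runs per setting, ρ = 0.5:

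| Pretest difference between arms | Joint MANOVA | ANCOVA |
|---|---|---|
| 0 SD | 1.4% | 4.9% |
| 0.3 SD | 4.7% | 4.9% |
| 0.4 SD | 13% | 5.2% |
| 0.5 SD | 56% | 4.7% |

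The standard error of the pretest difference is √(2/45) = 0.21 SD. A difference of at least 0.4 SD (z = 1.90) occurs in about 6% of randomizations, and one of at least 0.5 SD (z = 2.37) in about 2%. Averaged over all randomizations, the joint MANOVA still rejects 5% of the time.

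**The case against.** The strongest reply is that the protocol never says which variables enter the model. The document is a condensed article, and model detail commonly sits in an analysis plan that is not shown. It also promises a between-group comparison of scores, and its interest in both within-group and between-group comparisons fits a group-by-time analysis, which is valid. This largely stands: the figures for joint outcomes belong to one reading only. It does not rescue the choice, because the article does fix the method, and neither reading matches ANCOVA at the correlations tried.

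Four stronger conclusions are tempting, and the documents do not support them.

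- **That the test is invalid.** A reader might infer this from the 13% and 56% rejection rates. Those rates are conditional on uncommon imbalances, and the overall type I error is 5%.
- **That the pretest is wasted or left unadjusted.** The text does not say how the pretest is used. A joint MANOVA does use its information: at ρ = 0.5 and 0.7 it beats a posttest-only t test (80.4%), and it falls below that test only at low correlation.
- **That ANCOVA makes 90 students worth 120.** At ρ = 0.5, 90/(1 − 0.25) = 120 compares ANCOVA with an unadjusted posttest test. Against the joint MANOVA the figure is about 110.
- **That the questionnaires would remove the control arm from the analysis.** No section puts them into the MANOVA or says that only the intervention arm completes them, though their content makes that likely. The descriptive statistics already named can serve them.

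**Conclusion.** The point holds as a poorly matched and underspecified choice of method, not as an invalid analysis. Read as joint outcomes, the multivariate ANOVA does not isolate the posttest effect, can respond to a chance pretest difference, and gives up about 3 to 9 points of power against ANCOVA. Read as group by time, it is sound but gives up about 2 to 18 points (97.6 − 95 to 83.9 − 66). At a correlation of 0.5, ANCOVA passes the protocol's 85% target with the planned 90 students and neither reading of the plan does.

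The power figures rest on 0.6 being Cohen's d, a two-sided 5% test and an assumed correlation of 0.3 to 0.7. The advantage of ANCOVA shrinks as the correlation rises. That the omnibus test does not isolate the posttest contrast depends on none of these assumptions.

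**What to change.** In the Data Analysis Plan, name the primary analysis: an ANCOVA of posttest MCQ score on arm, with pretest MCQ score as covariate and center as a factor, because allocation is balanced 15 to 15 within each center. Report the adjusted mean difference with its 95% CI. Present within-group pretest-to-posttest changes descriptively. Report the two questionnaires on the immersive reality system descriptively and keep them out of any between-arm multivariate test. If a multivariate ANOVA is kept for another purpose, list its outcomes and label it secondary.

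The cost is a few sentences: the pretest and center are already recorded, and ANCOVA is standard in the named software. The article reports data collection as ongoing with the third center still to recruit, so the change is best dated and made before the outcome data are compared by arm.

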### Ethical Considerations

This study was approved by the Ethics Committee of the Faculty of Dentistry at Hasanuddin University in Makassar, Indonesia, in October 2024 (approval 001/KEPK FKG-RSGMP UH/EE/IX/2024). Written consent was obtained from all participants, and they were also assured that their information would be kept completely confidential. This manuscript is in accordance with the SPIRIT 2025 guidelines (Multimedia Appendix 6) [47].

## Results

Study enrollment started in May 2025 and is expected to be completed in November 2025. As of October 2025, we have enrolled 60 participants from two centers (Hasanuddin University, Makassar, and Padjajaran University, Bandung) and will continue recruiting from a third center (Universitas Sumatera Utara, Medan).

The trial was registered in the Indonesian Clinical Research Registry (INA-QES4CC5) on November 18, 2024.

## Discussion

### Strengths and Limitations

This study uses IR technology to advance the training of dental students in dental extraction methods, allowing them to experience immersive, high-fidelity scenarios that closely resemble actual clinical situations. One of the primary strengths of the IR training program is its incorporation of essential procedures for both open and closed extraction. The adaptation and validation process involves a thorough selection procedure conducted in collaboration with engineering experts. Consequently, the findings will offer both quantitative and qualitative perspectives on the enhancement of participants’ abilities. Moreover, the research included dental students from three distinct provinces (West Sumatra, West Java, and South Sulawesi) to provide an in-depth analysis of the potential influence of IR-based training on dental students’ skills in performing tooth extractions.

The presence of a control group in this study enables the observation of improvements in dental students. The pre- and posttest MCQs allow not only comparisons within the same group but also evaluation of the IRTS against traditional methods regarding dental students’ learning outcomes, thereby strengthening the validity of our findings.

In recognizing the strengths of this study, it is equally crucial to address its limitations. A notable concern is the potential for selection bias, as participants may inherently possess a favorable disposition toward technology or virtual reality environments. To mitigate this bias, we have meticulously documented the participants’ prior interactions with virtual reality technology and incorporated this information into experience distribution tables.

### Challenges

One of the primary challenges in this study is the adaptation of the IR environment to align with actual dental extraction procedures. The IR environment differs from conventional simulation in its representation of communication and interaction, as certain elements, such as natural communication with patients and their relatives, may be absent, while others, including nonverbal cues and nuanced interpersonal behaviors, are often not effectively captured within the IR environment. To address this concern, the IRTS has been developed, featuring interactive questions aimed at enhancing students’ comprehension of patient diagnoses. Moreover, evaluators face the ongoing challenge of accurately observing and assessing participant behavior in an IR scenario. To consistently and objectively implement the IRTS, it is essential to have a clear and thorough understanding of participant behaviors, both as they occur in real time and through recorded observations. One significant challenge associated with the implementation of IR technologies in dental education is the cost of procurement [48]. However, recent publications indicate that while the initial investment in IR technology may be substantial, it offers the advantage of providing repeatable training without the need for physical materials. Consequently, it can be used in the long term to reduce the costs associated with practical models for tutorials and hands-on training [49]. As the technology becomes more affordable and user-friendly, its applicability in medical and dental training is expected to grow [49].

### Future Implications

In addressing certain limitations of the study, future research could investigate the incorporation of more advanced haptic devices and natural language processing to enhance the realism of the IR environment and more comprehensively capture the full spectrum of participant behavior. As IR technology continues to progress, it is imperative to consistently refine the tools used to ensure they remain congruent with the evolving capabilities of the technology.

## Data Availability

The datasets generated or analyzed during this study will be made publicly available after completion of the study and will be available from the corresponding author upon reasonable request.

## Appendix

Multimedia Appendix 1 Pretest and posttest multiple-choice questions.

Multimedia Appendix 2 Informed consent form.

Multimedia Appendix 3 Health status form.

Multimedia Appendix 4 Clinical Virtual Evaluation Questionnaire.

Multimedia Appendix 5 Immersive Reality Neuroscience Questionnaire.

Multimedia Appendix 6 SPIRIT 2025 checklist.

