**Results:**

As of September 2025, 60 students from Hasanuddin University, Makassar, and Padjajaran University, Bandung, have been enrolled, and study enrollment will be expanded to Universitas Sumatera Utara, Medan. Data collection is ongoing and will conclude in November 2025, with expected dissemination in early 2026.

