#### Blinding and Calibration of Reviewer

Two independent reviewers (an oral and maxillofacial surgeon) were assigned to evaluate and score each participant’s pretest and posttest sheets (Multimedia Appendix 1). Before data collection, the assessors underwent a calibration session to standardize the answer key for the multiple-choice questions (MCQs) and ensure consistent scoring. During the study, the assessors were blinded to the participants’ identities and allocation status, as they did not have access to names or group assignments. A final score for each participant was calculated.

Additionally, the reviewer will assess the participants’ training videos, focusing on training time completion, in-app lag or confusion, and skipped steps, to evaluate participants’ performance during training.

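### The MCQ compared between arms is attached to an article dated 5 November 2025, when up to 30 of the 90 students may not yet have been tested

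*Protocol article*

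**What the plan says.** The title block of the protocol article gives 5 November 2025 as the publication date. The Appendix list includes "Multimedia Appendix 1 Pretest and posttest multiple-choice questions". Under Blinding and Calibration of Reviewer, the two assessors are to "score each participant’s pretest and posttest sheets (Multimedia Appendix 1"), so the attachment is presented as the scored instrument. Its role is set out under Participants' Performance and Knowledge Improvement: "The scores ranged from 0 to 100, and the test scores of both groups were subsequently compared". The same section says that the examination already belongs to the curriculum at all three universities.

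On timing, the Results section states "As of October 2025, we have enrolled 60 participants from two centers" and that the investigators "will continue recruiting from a third center (Universitas Sumatera Utara, Medan"). The Abstract adds: "Data collection is ongoing and will conclude in November 2025". Table 1 places the posttest MCQ at closeout, also November 2025. The Overview gives 15 students per arm within each of three centres. The article mentions no embargo on the appendix and no different test for the third centre.

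**The concern.** A knowledge test measures the effect of training only if the students have not prepared from its items. On the stated timeline, the items become public before or during testing at one whole centre.

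Prior sight of the items would raise scores for reasons unrelated to training. If it happens before the pretest, baseline scores rise and there is less room to gain. If it happens in both arms, posttest scores crowd towards the top of the scale and the difference between arms at that centre shrinks. The pooled difference then understates the contrast seen at the other two centres. The pretest at that centre would also mean something different from the pretest elsewhere.

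Blinding the assessors gives no protection, because the problem lies with what the student has seen. The MCQ score is the outcome that the article explicitly says is compared between groups, and its discussion of strengths rests validity on the pretest and posttest comparison.

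**Working it through.** **Number of students who could be affected.** Planned total 90 (Overview). Enrolled at the last dated count 60, from two centres (Results). Outstanding: 90 − 60 = 30, which equals one centre of 15 + 15. Share: 30/90 = 33.3%. This is an upper bound. The last status is for October, and any third-centre student who finished both tests before 5 November is not affected.

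**Order of events.** October 2025: third centre still to be recruited. 5 November 2025: article and appendix published. November 2025: end of data collection and, in Table 1, the posttest. Testing at the third centre can fall after publication, but the article does not show how much of it does.

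**The plan's own sample size.** The Overview gives effect size 0.6 and power 85% for a total of 90. Reading 0.6 as Cohen's d with alpha 0.05, an exact t-test needs 51 per arm (102 in total) two-sided, or 41 per arm (82) one-sided. With 45 per arm, power is 80.4% two-sided and 88.1% one-sided. The stated combination is not reproduced. That is a separate matter and this point does not depend on it. The illustration below starts from the two-sided 80.4%.

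**Illustration of dilution.** Assumptions, not taken from the article: the true difference is 0.6 SD at the first two centres, it is k × 0.6 at the third, and the SD is unchanged. With equal centres, the pooled d = 0.6 × (2 + k)/3. Power comes from the noncentral t distribution with 88 degrees of freedom, noncentrality d × √(45/2) = d × 4.743, and a two-sided 5% test.

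| Contrast kept at third centre (k) | Pooled d | Noncentrality | Power |
|---|---|---|---|
| 100% | 0.60 | 2.846 | 80.4% |
| 50% | 0.50 | 2.372 | 65.0% |
| 0% | 0.40 | 1.897 | 46.7% |

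The last row requires the whole contrast at that centre to vanish. It is a limit, not a forecast.

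**Cost in precision of leaving out the third centre.** With 30 per arm and d = 0.6, two-sided power is 62.8%. The standard error grows by √(90/60) = 1.22, about 22%. If k = 0.5, the full analysis (65.0%) and the reduced one (62.8%) have nearly the same power. The reduced analysis is therefore a check on the estimate and not a substitute for the main result.

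**The case against.** The strongest reply is that nothing shows any student saw the items. The appendix is not available here, so its completeness, its language and whether it contains the key cannot be checked. The examination is already in the curricula at all three universities, so what matters is the exposure that publication adds, and that is unknown. These points stand. They are why no size can be claimed.

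A reader might infer that 30 students were in fact exposed. The article supports only a maximum of 30, because the status on 5 November is inferred from an October count. The Overview does say in the past tense that 90 students took part, but that sentence is undated and conflicts with the dated statements in the Abstract and Results.

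A reader might also infer bias towards one arm. Randomisation is within centre, so access is equal by arm, and exposure before randomisation is balanced in expectation. Students know which training they receive, so unequal looking-up between randomisation and posttest is possible. Nothing in the article suggests that it happened, and no figure for it can be derived.

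Nor is the MCQ the sole assessment. The article also plans a video review of completion time and skipped steps and does not confine it to the immersive arm.

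Finally, it may be said that a journal article leaves detail to the full protocol. That does not answer this point, which concerns two things the article itself states: the attachment of the instrument and the testing calendar.

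**Conclusion.** The point holds as a possible threat of unknown size. By the article's own dates, the instrument compared between arms becomes public while up to 30 of 90 students (at most 33%) may be untested. The likely consequences are a raised pretest, a ceiling effect and a smaller contrast at the third centre. The power range of 80% to 47% is correct arithmetic on an assumed retained contrast and says nothing about how likely each value is. Bias towards one arm is not shown. The point lapses if all third-centre students completed both tests before 5 November 2025. It is worth acting on because the safeguard is cheap and lets readers judge the result.

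**What to change.** 1. Record each student's pretest and posttest dates and report, by centre and arm, how many fell after 5 November 2025.
2. Make the main MCQ comparison within centre (stratified by centre), and pre-specify it with and without the students tested after publication, before the third centre's data are examined.
3. If third-centre students are still untested, the investigators may use a parallel form at that centre: same blueprint and textbook, key set by the same assessors, given to both arms at pretest and posttest. Because allocation is 15:15 within the centre, a form specific to that centre does not bias the comparison within it.

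Withholding the appendix is no longer an option once the article is out.

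Cost: steps 1 and 2 need a date field and one further analysis. The analysis without those students has up to 30 fewer. If they make up the whole third centre, a change in the estimate could also reflect a difference between centres, and the report should say so. Step 3 needs a new item set and a short key calibration. The forms would not be equated, so raw scores at that centre could be compared only within it.
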